### Sample size and power calculation

Bound by the limited resources, we took several steps to decide the sample size to simplify the management while promise the scientifically meaningful differences. We used Power Analysis and Sample Size (PASS, 11.0) to help us calculate the statistical power and sample size. A statistical power of 80% with 0.05 significance level was chosen.

(1) *Cases of continuity of clinical care*. First, we used *two independent proportion calculation* to estimate the continuous cases needed in terms of *continuity of clinical service* (see “Outcome”), which would mostly constrain the statistical power. The results showed that although 100 cases in the treatment group could promise a required power, with the uncertainty of sample size in control group, we needed at least 120 cases in the treatment group to detect a 20% difference between groups with required significance level (see Table 2). (2) *Sample size*. We decided the minimum sample size based on the knowledge of cases needed and previous data. According to the previous reimbursement records in trial place (2010–2012), the continuous cases accounted for 3.0–5.0% among the chronic hypertensive patients, so with a conservative consideration, we need at least 230–270 individuals per town (530/490 per group) to ensure that we could have 120 continuous cases in each group. (3) *Power calculation*. Third, according to the estimated sample size we re-calculated the statistical powers under other indexes to check out whether that the sample size was sufficient. We chose several main variables and analysis methods to calculate the possible statistical power and output the required odds ratios (see Table 3). (4) *Drop-outs*. Taking a conservative drop-out rate of 20%, we finally arrived at an estimated sample size of 258–324 per town.

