## Methodology

### Study design

A clustered randomised controlled trial was used. Nearly 60 clusters/villages in 6 towns and 200 professionals from three levels were intervened, and around 6000 chronic patients were enrolled in this trial. We re-designed the health policy by giving initials to change their delivery and payment system on chronic diseases. There were two basic intervention modes: (1) care integration (MDT and MIP), which was to integrate different caregivers aiming to reshape the solitaire county–town–village service frame into an integrated health care delivery system; (2) payment integration (SGB–P4P), which was to integrate between the delivery system and medical insurance payment system by alternating the original fee-for-service system into a pre-paid system. This strategy aimed to create incentives to help the suppliers to act more willingly or actively. In accordance, the 60 clusters were categorised into three groups: two treatment groups which implemented each of the above strategy; and one control group with no interventions to serve as a natural blank comparison.

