#### The exclusion criteria

The exclusion criteria were those who: (1) had a stable BP/GLU history (consistently under 120/80 mm Hg and 6.5 m mol/L) longer than one year and thus would not admit having chronic diseases or refuse to take medicines; (2) were estimated for a life expectancy less than two years due to old age, venerable situations or severe complications such as cerebral infarction or pancreatic cancer, thus would potentially call for apparent extra samples; (3) would probably get lost in follow-ups with high chances to go out, which was recognised for at least six months away yearly during the intervention period for reasons as migration for work, education or kinship-care-seeking; (4) would hardly visit or investigate due to intellectual or activity incompetence; (5) mentally damaged or communication incapable; (6) refuse to cooperate due to personal reasons. Newly recorded patients between intervention period were not in our sample giving that they would mostly be managed under risk level I and unnecessarily shake the sample structure.

Finally 1641 patients with hypertension and 332 with diabetes II of the total 6833 managed subjects were selected from the record list provided by the local administrator (see Table 4). At the baseline and end-line of this trial, we will take all the samples into statistical examination, checking out if there were any differences.

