**Table 2. tb0002:**
[figure not shown]
Minimum cases needed under index “continuity of clinical service”

Summary: group cases of 120/96 or 120/120 in treatment/control group could achieve over 80% power to detect a 0.2000 difference between group proportions.

^a^Considering the intervention effect, we assumed the relation of conforming cases between control/treatment group varied from 0.8–1.0/1.0.

^b^Assumed the detectable proportion of cases conformed to the defined “continuity of clinical service” is 0.5–0.7 in the treatment group and 0.3–0.5 in the control group.

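### The sample-size step cannot be right as written: 490–530 patients per group at a 3.0–5.0% share give about 15–27 continuous cases, not 120, so the 80% power stated for this index is unsupported

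*Protocol article*

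**What the plan says.** All of the sizing is in the Protocol article, under Sample size and power calculation, with a summary and footnotes at Table 2.

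- Target: "A statistical power of 80% with 0.05 significance level was chosen".
- Step (1) uses a comparison of two independent proportions "to estimate the continuous cases needed in terms of" continuity of clinical service, the index the authors expect to limit power most. It concludes that "we needed at least 120 cases in the treatment group to detect a 20% difference between groups".
- The Table 2 footnote says that the assumed proportion of conforming cases "is 0.5–0.7 in the treatment group and 0.3–0.5 in the control group". The table summary reports over 80% power with 120/96 or 120/120 cases (treatment/control).
- Step (2) turns cases into patients. From reimbursement records for 2010–2012, "the continuous cases accounted for 3.0–5.0% among the chronic hypertensive patients". The text then infers a need for 230–270 people per town, given as "530/490 per group) to ensure that we could have 120 continuous cases in each group".
- Step (3) checks other indexes at that sample size (Table 3, not shown). Step (4) adds drop-out to reach 258–324 per town.

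The achieved sample is reported under The exclusion criteria: "Finally 1641 patients with hypertension and 332 with diabetes II of the total 6833 managed subjects were selected".

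**The concern.** Step (2) is one multiplication: patients times share equals cases. The share, the group size and the resulting case count all stand in the running text, and they disagree by a factor of roughly 4.5 to 8. The text gives no accrual period, episode count or other multiplier to link them.

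The step matters because the whole sample size rests on it: the later steps take the group size from here as their starting point. If the case count is far below 120, the comparison on continuity of clinical service does not have the stated power. A null result on it could then be read as evidence of no effect when the trial had little chance of seeing one.

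**Working it through.** **Inputs.** Two-sided alpha 0.05 (sidedness is not stated, so two-sided is an assumption); difference 0.20; proportions 0.5 v 0.3, 0.6 v 0.4 and 0.7 v 0.5 from the Table 2 footnote; control/treatment case ratio 0.8 to 1.0 from the same footnotes; share 0.03–0.05; 490–530 patients per group; 1,641 hypertensive patients selected.

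**Step (1), the plan's own figure, reproduces.** For n cases per group at 1:1, with pooled variance,

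power = Φ{ [Δ√n − 1.96·√(2p̄(1−p̄))] / √(p1(1−p1) + p2(1−p2)) }.

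For 0.5 v 0.3, p̄ = 0.4. With n = 120 this is Φ{(2.191 − 1.358)/0.678} = Φ(1.23) = 0.89. Across the three pairs of proportions:

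| Cases, treatment/control | Power |
|---|---|
| 120/120 | 87.7–89.0% |
| 120/96 | 83.7–85.3% |
| 100/100 | 81.2–82.8% |
| 100/80 | 76.5–78.4% |

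This agrees with the Table 2 summary and explains the move from 100 to 120. The number of cases needed is sound.

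**Step (2), cases to patients, does not reproduce.**

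- Cases expected: 490 × 0.03 = 14.7 and 530 × 0.05 = 26.5, so about 15–27 per group against 120 stated.
- Patients needed for 120 cases: 120/0.05 = 2,400 and 120/0.03 = 4,000 per group.
- Share needed: 120/530 = 22.6% and 120/490 = 24.5%.
- Shortfall: 120/26.5 = 4.5-fold to 120/14.7 = 8.2-fold.

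**Power at the expected number of cases** (0.5 v 0.3, 1:1, two-sided, independent patients).

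- n = 14.7: Φ{(0.767 − 1.358)/0.678} = Φ(−0.87) = 0.19.
- n = 26.5: Φ{(1.030 − 1.358)/0.678} = Φ(−0.48) = 0.31.

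**Other readings of the same figures.**

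| Reading | Cases per group | Power |
|---|---|---|
| Share covers the whole trial, 490–530 patients | 15–27 | 19–31% |
| Same, one-sided 5% test (all three pairs of proportions) | 15–27 | 28–44% |
| Drop-out allowance counted in full (2 × 258 = 516 to 2 × 324 = 648) | 15–32 | not computed |
| Hypertensive sample, 1,641/3 = 547 if split equally | 16–27 | close to the first row |
| Share is annual, 24 months: 490 × 0.03 × 2 to 530 × 0.05 × 2 | 29–53 | 33–56% (all three pairs) |

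A control/treatment case ratio of 0.8 lowers the first row to about 17–29%. None of these figures allows for clustering, which would lower them further.

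**The case against.** The strongest reply is that the arithmetic shows a conflict but not which figure is wrong. The time base of the 3.0–5.0% is not given; the text says only that it comes from records of 2010–2012. A quarterly share over eight quarters would give 490 × 0.03 × 8 = 118 to 530 × 0.05 × 8 = 212 cases, and the plan would then roughly hold. This part of the objection stands: 19–31% is a conditional figure and should not be reported as the trial's actual power. But nothing in the article suggests a quarterly share, and an annual share over the 24 months under Trial status still leaves power well below 80%.

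A second reply is that Table 2 accepts 96 control cases, so 120 in each group is stricter than necessary. That is true, but 96 cases still need 96/0.05 = 1,920 to 96/0.03 = 3,200 patients.

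Three further inferences are tempting and are not supported:

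- **That the primary outcomes are underpowered.** Under Outcomes measures these are period BP/GLU control rate and drug compliance. Step (3) checks other indexes separately, and Table 3 is not shown. The error does not carry over to them by itself.
- **That the enrolment figures contradict each other.** Study design says "around 6000 chronic patients were enrolled in this trial", while far fewer were selected. The project is described as population-based, so the larger figure can be the managed population under intervention and the smaller one the sample for investigation and follow-up. The wording is loose, but an error is not shown.
- **That analysing all 6,833 managed patients would rescue the index.** The share is given for hypertensive patients only, and the article does not say that the reimbursement extract covers everyone managed.

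**Conclusion.** Wrong as written. A 3.0–5.0% share, 490–530 patients per group and 120 continuous cases per group cannot all be right. The error lies in converting cases to patients; the case target itself is correctly powered.

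The size depends on the unstated time base. With the share covering the whole trial, which is the plain reading, power for this index is about 19–31%. With an annual share it is about 33–56%. Both assume a two-sided 5% test and independent patients, and the first is for 0.5 v 0.3 with equal case numbers. The conclusion is confined to continuity of clinical service, the index used to size the trial.

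**What to change.** In Sample size and power calculation, step (2):

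1. Reconcile the share, the group size and the case count, and show the multiplication that links them.
2. State the period that the 3.0–5.0% refers to, and whether it counts patients or episodes.
3. Restate the expected continuous cases per group and the resulting power for this index.
4. Withdraw the assurance of 120 cases per group and the 80% power for this index unless the reconciled figures support them.
5. State that a null result on this index will be treated as inconclusive, and report the estimate with its confidence interval.

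If the authors wish, they can also label the population under intervention and the selected sample as two distinct groups.

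The cost is a text correction and, probably, a less favourable power statement for one index. No extra enrolment, new data or change to the analysis population is proposed.

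### The planned 258–324 patients per town does not follow from the stated minimum of 230–270 and a 20% drop-out rate

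*Protocol article*

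**What the plan says.** All the planning figures are in the Protocol article, under Sample size and power calculation.

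- **Target.** "A statistical power of 80% with 0.05 significance level was chosen". Step (1) concludes that "we needed at least 120 cases in the treatment group to detect a 20% difference between groups with required significance level". A Table 2 footnote adds that the assumed proportion meeting the continuity definition "is 0.5–0.7 in the treatment group and 0.3–0.5 in the control group".
- **Minimum sample.** Step (2) takes continuous cases to be 3.0–5.0% of hypertensive patients and states: "we need at least 230–270 individuals per town (530/490 per group) to ensure that we could have 120 continuous cases in each group".
- **Drop-out.** Step (4) reads: "Taking a conservative drop-out rate of 20%, we finally arrived at an estimated sample size of 258–324 per town". It names no base other than the preceding minimum.

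Two later sections bear on the point. Enrollment and masking says that patients lost during the intervention are not substituted. The exclusion criteria section closes with the sample obtained: "Finally 1641 patients with hypertension and 332 with diabetes II of the total 6833 managed subjects were selected".

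**The concern.** A drop-out allowance has one purpose: after the expected loss, the number remaining should still meet the requirement. Here the allowance is too small at both ends of the range, and the two ends do not come from the same rule. Because lost patients are not replaced, this allowance is the only margin the plan states against attrition.

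At stake is whether the final sample size, which readers will take as the trial's justified size, delivers the minimum that the same paragraph calls necessary.

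**Working it through.** **Inputs.** Minimum 230–270 per town (step 2); drop-out 20% and final figure 258–324 per town (step 4); six towns in three groups, so two towns per group (Sampling and randomisation); 1,641 hypertension and 332 diabetes patients selected (end of the exclusion criteria).

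**1. Is the fault upstream?** A two-sided test of two proportions at 0.05, with the Table 2 proportions (0.5 v 0.3, 0.6 v 0.4, 0.7 v 0.5), gives power of 83.7–85.3% for 120/96 cases and 87.7–89.0% for 120/120. The article does not state sidedness; two-sided is assumed. Table 2's claim of over 80% power is therefore reproduced, and the case count is not the source of the error in step (4).

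**2. Trying to reproduce 258–324.**

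| Base per town | n / (1 − 0.20) | n × 1.20 | Printed |
|---|---|---|---|
| 230 | 287.5, so 288 | 276 | 258 |
| 270 | 337.5, so 338 | 324 | 324 |

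The upper figure matches the multiplication by 1.2 exactly. The lower figure matches neither rule. As 258/230 = 1.122, it implies a loss of 1 − 230/258 = 10.9% by division or 12.2% by multiplication. It can also be written as 215 × 1.2, but 215 appears nowhere. Starting from half the per-group figures (490/2 = 245 and 530/2 = 265) gives 307 and 332 by division or 294 and 318 by multiplication, which does not match either.

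**3. What the printed figure retains after 20% loss.**

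- 258 × 0.8 = 206.4, against 230: short by 23.6 per town.
- 324 × 0.8 = 259.2, against 270: short by 10.8 per town.

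**4. What the selected sample retains after 20% loss (averages over towns).**

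| Patients counted | Per town | Per town after loss | Per group after loss |
|---|---|---|---|
| All: 1,641 + 332 = 1,973 | 328.8 | 263.1 | 526.1 |
| Hypertension only: 1,641 | 273.5 | 218.8 | 437.6 |

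The first row assumes that no patient is in both counts. The article's Trial introduction allows for patients with both diseases, so overlap is possible and would pull the first row towards the second.

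**5. Does the base of 230–270 hold?** At the stated 3.0–5.0%, 120 cases per group need 120/0.05 = 2,400 to 120/0.03 = 4,000 patients per group. The stated 490–530 per group would yield 490 × 0.03 = 14.7 to 530 × 0.05 = 26.5 cases. The minimum does not follow from its own inputs as printed. This is separate from the drop-out step and does not rescue 258–324, but it makes any corrected range conditional.

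**The case against.** **The allowance is deliberately generous.** The article calls 20% conservative, and its eligibility rules require stable residence and exclude people likely to move away. The printed figures would still hold the minimum at lower loss: 324 keeps 270 at up to 16.7%, and 258 keeps 230 at up to 10.9%. That is true and limits the practical risk. It does not make the calculation right at the rate the plan chose.

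**The selected sample may be large enough.** A reader might infer that the trial's sample will fall below its own minimum after drop-out. The documents do not support that in general. If all 1,973 patients count, about 263 per town remain, which is above 230 and below 270; per group, 526 is above 490 and 4 short of 530. Only a hypertension-only count (219 per town, 438 per group) falls below every stated minimum. That reading is plausible, because the 3.0–5.0% rate is given for hypertensive patients, but the minimum is worded for individuals. This objection stands, so the shortfall applies to the planned 258–324.

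**The per-group pair looks inconsistent but need not be.** Two towns of 230–270 give 460–540 per group, and a reader might infer that "individuals per town (530/490 per group") is an error. Both numbers lie inside that span and can be reached from towns in range (230 + 260 = 490; 260 + 270 = 530). Table 2 uses a slash for treatment/control, so this may be a pair of group totals. It is at most unclear notation and needs no replacement.

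**Little changes in cases or in shown power.** At 3–5%, 11 to 24 fewer patients per town is roughly 0.3 to 1.2 continuous cases. No loss of power on the primary outcomes (period BP/GLU control and drug compliance) can be shown, because Table 3 is not available. This stands and argues against a high grade.

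**Conclusion.** The point holds for the planned figure. With the stated minimum and the stated drop-out rate, 258–324 per town should read 288–338. The printed range is 30 too low at the lower end and 14 too low at the upper end. The upper end is a recognisable slip; the lower end has no stated derivation.

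The conclusion rests on 230–270 being the base for step (4), the only per-town base given, and on drop-outs not being replaced, which the article states. It does not establish that the realised sample is inadequate or that the primary outcomes are underpowered. For the selected sample, the result depends on who counts towards the minimum and on whether the two disease counts overlap. Table 4, with the town-level counts, is not shown, so the per-town results are averages.

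This is a correction that should be made, of modest practical size. The mismatch between 120 cases and a 3–5% case share is much larger and should be examined at the same time.

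**What to change.** 1. In step (4), restate the drop-out-adjusted size as 288–338 per town, and say that it is conditional on the 230–270 minimum. Alternatively, keep 258–324 and state that it retains only about 206–259 per town after 20% loss. If 258 had another base, give it.
2. Check the 230–270 minimum, showing how 120 continuous cases per group arise from it when the stated 3–5% share would call for 2,400–4,000 patients per group.
3. Report the expected analysed number from the sample actually selected: about 263 per town if all 1,973 patients count, or about 219 if only the 1,641 hypertensive patients do. Say which applies and whether the two counts overlap, and restate power on that basis.

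The per-group 530/490 can stay; a few words on what the slash means would help. Baseline data were collected and patients selected before publication, so the change affects reporting only. It costs text and a recalculation, with no change to trial conduct.

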### Sampling and randomisation

Six towns were selected randomly from the 24 rural communities and then were categorised into three groups with a combined consideration of population size, social development and distance. Because there were obvious potential confounders in social experiment, the towns were first categorised into two types based on comprehensive consideration of socio-economic development level and hospital ability, two basic confounders which we assumed high relevance with the intervention outcome. The socio-economic development level mainly indicated the patient population, their per capita income and average distance from the location to downtown (translated into traffic time by public transportation). The hospital ability represented resource possession and staff skills. Second, every two towns of each type were randomly assigned into treatment/control groups to ensure group comparability. These two steps were done to make sure towns comparable both within groups and within cluster types in case of different comparison need.

In patient sampling, we used three-stage stratified random sampling strategy instead of propensity scoring matching, concerning the complexity of sampling and excessive workload. We chose gender, age and risk level as the three stratify factors. Risk level was a comprehensive factor that summing up the BP/GLU level as well as the possible risky factors due to the patient lifestyle. The hypertension and diabetes II patients were divided into three and two risking groups before the baseline, and we stratified the patient library mainly in accordance with the original files but with a slight alternation based on professional re-assessment after personal contact at the baseline.

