**Table 4. tb0004:**
[figure not shown]
Result of grouping and patient sampling

Note: ① Type A for better cluster: larger and richer; type B for worse cluster: smaller and poorer. ② H for hypertension; D2 for diabetes 2. ③ Population, patient population and sample size are not averaged under “total average”. ④ All variables are compared with treatment group 1. ⑤ Distance is transferred into traffic time by public transportation. Time varies in accordance to the cluster terrain instead of linear map distance.

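### With six towns over three groups and two types, the allocation cannot support formal comparisons of arms within a town type, although the article reserves them

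*Protocol article*

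**What the plan says.** The Sampling and randomisation section describes the allocation. "Six towns were selected randomly from the 24 rural communities and then were categorised into three groups". Before assignment, "the towns were first categorised into two types based on comprehensive consideration of socio-economic development level and hospital ability". Then "every two towns of each type were randomly assigned into treatment/control groups to ensure group comparability". The purpose given for the two steps is "to make sure towns comparable both within groups and within cluster types in case of different comparison need". The note to Table 4 defines the types: "Type A for better cluster: larger and richer; type B for worse cluster: smaller and poorer".

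The Study design section gives the arms as "two treatment groups which implemented each of the above strategy; and one control group with no interventions", and counts nearly 60 villages, called clusters, in the six towns. The Statistical analysis section plans a difference-in-differences regression with group, time and their interaction. Its three levels are individual, village and group. Neither that section nor the Hypothesis section specifies an analysis by town type.

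**The concern.** The sentence on purpose goes beyond describing how towns were balanced. It offers the allocation as a basis for further comparisons, including comparisons within a town type. A comparison of arms needs some measure of how much towns under the same arm differ from one another. If a type holds only one town per arm, that measure does not exist, and the contrast between two arms is the contrast between two particular towns.

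What is at stake is how type A and type B results may be read. If the planned model were run within a type, it would still return a p-value, based on village and patient variation. A difference between two towns could then be reported as an effect of the package in poorer or richer towns, or as effect modification by type.

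**Working it through.** **Inputs.** From Sampling and randomisation: 6 towns, 3 groups, 2 types, town as the unit assigned, assignment within type. From Study design: about 60 villages in 6 towns, so about 10 per town. From Sample size and power calculation: 230–270 individuals per town and 530/490 per group. From the exclusion criteria section: 1641 + 332 = 1973 sampled patients. From Statistical analysis: levels individual, village and group, with no town level.

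**The plan's own figure.** The article gives no figure for within-type comparisons. Its Table 2 summary (over 80% power for a 0.20 difference with 120/96 or 120/120 cases) reproduces: 0.837–0.853 and 0.877–0.890 for a two-sided test at 0.05. That calculation treats cases as independent and says nothing about the number of towns.

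**Step 1: layout.** Two towns at 230–270 each come to 460–540, which fits the 530/490 per group, so two towns per group is consistent. On the balanced reading:

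- towns per group = 6/3 = 2
- towns per type = 6/2 = 3
- towns per group within a type = 6/(3 × 2) = 1

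**Step 2: residual degrees of freedom at town level** (number of towns minus rank of the model).

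| Comparison | Towns | Rank | Residual df |
|---|---|---|---|
| Group, within one type | 3 | 3 | 0 |
| Group × type, all six towns | 6 | 6 | 0 |
| Group + type, all six towns | 6 | 4 | 2 |

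Adding town indicators to the first model leaves its rank at 3, so within a type group and town are fully aliased.

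**Step 3: other layouts.** There are six towns and six cells. A second town in one cell leaves another cell empty. Either every arm appears in both types with one town each, or some arm is missing from a type. No layout gives all three arms in both types with any cell replicated.

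**Step 4: what the villages and the model can add.** Every village in a town has that town's arm, so villages inform on variation inside towns only. Difference-in-differences removes stable differences between towns. Within a type it leaves group × time aliased with town × time.

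**Step 5: illustration of size.** Assumptions not in the article: village intracluster correlation ρv = 0.01–0.03 and town intracluster correlation ρt = 0.005–0.05, cross-sectional. Patients per village m = 27 (270/10) to 33 (1973/60). For one town against one town, tested on village variation alone:

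- v = [ρv + (1 − ρv − ρt)/m]/10
- r = (ρt + v)/v
- error rate = 2 × [1 − Φ(1.96/√r)]

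Example with m = 33 and ρv = ρt = 0.02: v = [0.02 + 0.96/33]/10 = 0.00491; r = 0.02491/0.00491 = 5.07; error rate 38%.

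| ρt | Error rate of a nominal 5% test |
|---|---|
| 0.005 | 14–19% |
| 0.01 | 22–30% |
| 0.02 | 33–43% |
| 0.05 | 51–60% |

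**The case against.** The strongest reply is that no within-type test is planned. The Hypothesis section names two contrasts, treatment against control and one treatment group against the other, and the regression has no type term. The reply stands, and it limits the point to a comparison that the article reserves.

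A second reply is that towns can be comparable in the sense of being alike on income, size, distance and hospital ability, which is what sorting by type aims at. That also stands. A reader might infer that comparability within types does not exist at all. The article does not support this, because zero residual degrees of freedom rule out formal inference within a type but not similarity on measured factors.

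Third, the error rates rest on assumed correlations, span a wide range, and are cross-sectional, whereas the plan analyses change over time. Stable features of a town, such as its terrain, largely drop out of a difference-in-differences contrast, so the relevant town correlation may be smaller. The percentages are therefore not a property of this plan. The aliasing does not depend on them.

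Fourth, the exact layout is inferred, since the assignment sentence is loose and the body of Table 4 is not shown. This stands as a caveat, but Step 3 shows that no other layout rescues the reserved comparison.

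A reader might also infer that the overall comparison has no town-level error term. That is not so: 2 residual degrees of freedom remain under the group + type model.

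**Conclusion.** The point holds for comparisons of arms within a town type. On the balanced reading there is one town per arm within each type, group is fully aliased with town, and 0 residual degrees of freedom remain, both within a type and for group × type over all six towns. This follows from the article's own counts and needs no assumed correlation.

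The planned model has no town level, so its p-values within a type would omit town variation. Under the assumed cross-sectional correlations the error rate of a nominal 5% test would be about 14–60%; for change over time it could be lower. The weight is moderate: the comparison is reserved and not the main one, but the article presents the design as serving it.

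**What to change.** In Sampling and randomisation, withdraw cluster type as a basis for comparing arms and keep it as the allocation stratum. State that type A and type B results will be reported descriptively, as profiles of towns, without p-values or claims of effect modification by type. Base tests of effect on all six towns with town as the unit of assignment, and state that the group + type model leaves only 2 residual degrees of freedom at town level (two-sided 5% critical value of t = 4.30).

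This takes a few sentences and no new data, and no valid within-type inference is lost. The downside is that the trial can draw no formal conclusion by town type.
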